**Figure 1 F1:**
[figure not shown]
Design of the study.

### Questionnaires

The questionnaire set consists of three different questionnaires and some additional background questions for case-mix adjustment and to identify possible determinants of a change in the levels of patient-centeredness, patients’ QoL and distress levels.

#### Patient-centredness Questionnaire – Infertility

The Patient-centredness Questionnaire – Infertility, a validated instrument measuring patient-centeredness of fertility care by asking about patients’ experiences with care, is composed of 46 questions. This questionnaire contains seven subscales, namely: Accessibility, Information, Communication, Respect for patients’ values, Continuity and transition, Patient involvement, and Competence
[18]. A higher score on the total Patient-centredness Questionnaire scale or one of the subscales represents a higher level of patient-centeredness.

#### FertiQoL questionnaire

The internationally developed and validated FertiQoL questionnaire consists of two general items and two modules measuring QoL (the FertiQoL Core and the optional FertiQoL Treatment module). The Core module involves 22 fertility-specific items covering four subscales; Mind–Body, Emotional, Relational and Social. The optional treatment module assesses QoL related to the fertility treatment itself. In this study the Dutch version of the two general items and the FertiQoL Core module will be used. A higher score on the total FertiQoL scale or one of the subscales means better QoL
[27].

#### SCREENIVF questionnaire

The recently developed SCREENIVF questionnaire consists of 31 questions covering five emotional maladjustment scales (that is, five risk factors for increased emotional problems during fertility treatment); anxiety, depression, helplessness, acceptance regarding fertility problems, and perceived social support
[30]. The assessments of anxiety, depression and perceived social support are based on generic instruments (that is, Spielberger State and Trait Anxiety Inventory
[31,32], Beck Depression Inventory
[33], and Inventory of Social Involvement
[34], respectively), and the assessments of helplessness and acceptance are based on a fertility specific instrument (that is, Illness Cognition Questionnaire
[35,36]). Subscale scores will be calculated according to the cutoff values described by Verhaak and colleagues
[30]. Based on these five subscales, total SCREENIVF scores range from 0 to 5, indicating how many risk factors for increased emotional problems during fertility treatment are present
[30].

### The intervention

Clinics randomized for the multifaceted approach will be exposed to this intervention for 1 year. The content of the multifaceted approach is based on previous interviews with Dutch gynecologists, fertility nurses and hospitals’ quality officers about their potential barriers and facilitators for quality improvement, and on previous studies on patient-centered fertility care
[19,37,38]. These studies reported a large variation between clinics and the need for feedback about current performance for the clinicians involved
[18,19]. However, it is shown that audit and feedback alone is not enough; the effectiveness increases if feedback is detailed, offered in high intensity, with professionals’ involvement and as part of a multifaceted intervention
[39-42]. We therefore designed a multifaceted approach consisting of three elements: audit and feedback, educational outreach visits (EOVs), and patient-mediated interventions.

The feedback consists of a personalized paper report with the clinic’s own results, benchmarked and presented in relation to all 32 participating clinics. To identify aspects of care with priority for improvement, quality improvement scores will be calculated per clinic and presented in the feedback report. The higher a quality improvement score (3 – perceived experience score × importance score from the patients’ perspective), the more need there is for improvement
[18]. The clinics receive this report shortly after baseline measurement and 1 month before the EOV will take place. Prior to this visit, the researcher and representative gynecologist will discuss the results from the baseline measurement and define the most important items for EOV.

During EOV, the feedback reports will be discussed with the team of each clinic exclusively paying special attention to their high quality improvement scores. The EOVs are led by a researcher involved in baseline measurement and drafting the feedback reports. For the EOV, all members of the fertility team (gynecologists, residents, nurses, secretaries, embryologists, analysts) will be invited. Each EOV results in the definition of improvement goals and a clear action plan with allocation of tasks defined by the professional team. The EOVs will also be attended by a quality officer of the hospital involved, who will manage the execution of the formulated action plan. Additionally, a representative of the Dutch Patients’ Association of Infertility ‘*Freya*’ who is a former patient of that clinic will be present. These representatives can present the needs and wishes of infertile patients during the EOV. All patients’ representatives will receive a manual about EOVs and undergo a short training program for fulfilling their role in the EOV.

Finally, to enable clinics to translate items mentioned in the feedback report to the clinic’s daily reality they are offered several patient-mediated interventions. For example, clinics can decide to organize focus groups or create online communities to gain more specific and detailed information from their patients about the care aspects with the highest quality improvement scores.

Following the EOV, the hospital’s professional team and quality officer will be mainly responsible for the execution of the action plan. However, the researchers will monitor this process carefully by contacting the team every 2 months. Additionally, all professionals and representatives of *Freya* are invited to participate in an online study community. This community will be a platform for professionals to exchange their ideas about quality improvement programs. Besides, the researcher will write a blog at least every 2 months in which the quality improvement progress of all participating clinics will be described. The ideas and progress of one clinic can stimulate another clinic to improve even more.

### Determinants of change in patient-centeredness, patients’ QoL and distress levels

#### Patient characteristics

The following patient characteristics will be collected, based on general and fertility literature as possibly being associated with patient-centered care, QoL and/or levels of distress: gender, age, ethnicity, level of education, duration of relationship, economic status, duration and cause of infertility, fertility treatments so far received, consumption of professional emotional support during fertility treatment, medical history, and recently experienced lifetime events (for example, death of a relative, being fired from work)
[18,43-46].

#### Clinic characteristics

Potential determinants at the clinic level will be collected by a professionals’ questionnaire during patients’ baseline measurement and by separate data collection during the EOV. The questionnaire will be spread electronically among all healthcare professionals (for example, gynecologists, residents, nurses, laboratory employees, secretaries, and so forth) working at the fertility departments of the 32 participating hospitals. The questionnaire consists of two parts: 12 general questions about clinic characteristics (for example, number of fertility consultations per year, composition of the fertility team, mean age and sex ratio of the fertility team); and six questions from the Organizational Culture Assessment Instrument, a validated questionnaire to examine organizational culture based on the Competing Values Framework
[47-49]. The Competing Values Framework recognizes that no hospital exhibits only one culture, but that multiple cultures and values coexist simultaneously
[50] (that is, clan/family culture, adhocracy culture, market culture, and hierarchy culture). The four culture types relate to each other on a two-by-two matrix with two axes denoting both the flexibility and the orientation of the hospital to the outside world
[47-49,51-53]. In this study the validated Dutch version of the Organizational Culture Assessment Instrument will be used
[54].

Additional possible determinants at the clinic level of a change in patient-centeredness, patients’ QoL and distress levels will be collected during the EOV. According to the literature, these characteristics may influence successful implementation of the action plan – such as, for example, the level of preparation before and the enthusiasm and agreement of the professional team during the EOV
[55]. The researcher will record these team characteristics on a five-point Likert scale.

### Sample size calculation

To account for a representative number of patients per clinic (that is, 25 to 75 patients per clinic) at least 1,600 couples will be included. The sample size calculation, which was based on the results of the previous Patient-centredness Questionnaire validation study
[18], confirmed that this number of patients is sufficient for a proper analysis. To detect a mean difference score of 0.25 between usual care and the multifaceted approach on patient-centeredness (α = 0.05, two-sided testing, β = 0.8) at least 93 couples are required. Taking into account clustering of couples (30 couples/clinic) and a mean intracluster correlation coefficient of 0.13
[18], 1,023 couples have to be involved. With an expected response rate of 70%
[18], at least 1,462 couples have to be invited at both baseline and after measurement.

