### Study population

The study will be performed in a representative Dutch infertile patient group, under treatment in one of 32 Dutch clinics. All couples that participate in this study underwent at least one cycle of medically assisted reproduction (for example, ovulation induction, intra-uterine insemination, IVF, and intra-cytoplasmic sperm injection). Both women and their partners will be invited to participate in this study individually. However, because it is still unknown whether women and partner experiences with patient-centered fertility care are associated, only the women’s data will be used to answer our main research questions. Partners’ data will be used to analyze whether gender is a determinant of patient-centered fertility care. Those couples who are pregnant while completing the questionnaire set will be excluded from all analyses, because most questions about patient-centeredness, patients’ QoL and levels of distress are confounded in this patient group
[18,27,28].

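### The 1,023 couples do not follow from the stated 93 couples, 30 per clinic and ICC 0.13; the inputs and the total need reconciling, although the discrepancy errs on the safe side.

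*Protocol article*

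**What the plan says.** Everything is in one paragraph of the protocol article, Methods/Design, Sample size calculation. The target is set out as "To detect a mean difference score of 0.25 between usual care and the multifaceted approach on patient-centeredness", with error rates "α = 0.05, two-sided testing, β = 0.8". Before clustering, "at least 93 couples are required"; the text does not say whether this is per arm or in total. The adjustment is then "Taking into account clustering of couples (30 couples/clinic) and a mean intracluster correlation coefficient of 0.13", and the result reads "1,023 couples have to be involved. With an expected response rate of 70" per cent, which leads to at least 1,462 invitations at each of the two measurements.

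The same paragraph opens with a planned minimum of 1,600 couples, at 25 to 75 per clinic, and presents the calculation as confirmation that this number is enough. The Study design section fixes 32 clinics, 16 per arm, and explains that the 25 to 75 patients per clinic are selected and then sent an invitation. The Study population section adds: "Those couples who are pregnant while completing the questionnaire set will be excluded from all analyses".

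**The concern.** The paragraph prints a starting number, a cluster size, an ICC and a result, so a reader can check the clustering step directly. It fails on either meaning of 93. This calculation is the article's only stated support for the claim that the planned number is sufficient. The minimum number of invitations for the follow-up measurement also comes from it. The Trial status section says the intervention had only just started, so that measurement still lay ahead and a corrected figure could be used. As printed, a reader cannot tell which input or output is wrong, or what power the trial was designed to have.

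The power label adds to the confusion. Read literally, a beta of 0.8 means 20% power; power of 0.80 (beta 0.20) is evidently meant.

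**Working it through.** **Inputs.** From the Sample size calculation: difference 0.25; two-sided alpha 0.05; power 0.80 (printed as beta); 93 couples before clustering; m = 30 couples per clinic; ICC = 0.13; response 70%; printed results 1,023 and 1,462. From the Study design: 32 clinics, 16 per arm.

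**The step that reproduces.** 1,023 / 0.70 = 1,461.4, rounded up to 1,462. The non-response step is correct.

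**The step that does not.** Design effect DE = 1 + (m − 1) × ICC = 1 + 29 × 0.13 = 4.77.

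| Reading of 93 | Before clustering | × 4.77 | Invitations at 70% | DE implied by 1,023 | m needed at ICC 0.13 | ICC needed at m = 30 |
|---|---|---|---|---|---|---|
| Total | 93 | 443.6, so 444 | 635 | 1,023 / 93 = 11.0 | about 78 | about 0.345 |
| Per arm | 186 | 887.2, so 888 | 1,269 | 1,023 / 186 = 5.5 | about 35.6 | about 0.155 |

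**Variants with the stated inputs** (total reading / per-arm reading):
- DE = 1 + m × ICC: 456 / 911.
- Whole clinics in equal arms: 480 / 900.
- One extra clinic per arm: 540 / 960.
- Clinics fixed at 16 per arm, per-arm reading: 93 × 0.87 / (16 − 93 × 0.13) = 20.7 per clinic, or 662 in all.

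None comes within 3% of 1,023.

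**Inputs that would reach it** (per-arm reading), none of them stated for this step:
- 35 per clinic: 186 × (1 + 34 × 0.13) = 1,008.
- 36 per clinic: 186 × (1 + 35 × 0.13) = 1,032.
- 30 per clinic with a coefficient of variation (CV) of clinic size of 0.43: DE = 1 + ((1 + 0.43²) × 30 − 1) × 0.13 = 5.49, giving 1,021.

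**Clinic count.** 32 × 30 = 960, which is below 1,023. The stated cluster size cannot deliver the stated total in the stated number of clinics.

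**Power of the actual plan.** The article gives no SD, so I back-calculate it from n per arm = 2 × (1.96 + 0.8416)² × SD² / 0.25². With 93 per arm, SD = 0.61; with 46.5 per arm, SD = 0.43. I take 1,600 as the number invited (32 clinics at an average of 50). Then 1,600 × 0.70 = 1,120, or 35 per clinic and 560 per arm, and DE = 1 + 34 × 0.13 = 5.42.
- Per-arm reading: effective n per arm = 560 / 5.42 = 103.3; SE = 0.6085 × √(2 / 103.3) = 0.0847; 0.25 / 0.0847 − 1.96 = 0.99; power about 84%.
- Total reading: about 99%.
- Unequal clinics, per-arm reading: if sizes are spread evenly over 25 to 75 (an assumption), CV = (50 / √12) / 50 = 0.29. DE = 1 + ((1 + 0.29²) × 35 − 1) × 0.13 = 5.80; effective n per arm = 96.5; power about 81%.

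**The case against.** The strongest reply is that nothing in the plan depends on the faulty number. The plan commits to at least 1,600 couples, the calculation only confirms that this is enough, and the confirmation survives. There is also a plausible origin for 1,023: 1,600 invitations at 70% give 35 respondents per clinic, and on the per-arm reading 35 per clinic requires 1,008, within 1.5% of the printed total. On that view one cluster-size figure is out of step and the requirement itself is roughly right.

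Most of this stands, and it limits the point. It does not rescue the paragraph, because the text says 30 per clinic and mentions no allowance for unequal clinics.

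A reader might be tempted by several stronger readings that the article does not support:
- **That the requirement is 2.3 times too large.** This holds only if 93 is a total. On the per-arm reading the excess is 15% (1,023 against 888).
- **That 444 or 888 should replace 1,023.** That presumes 30 and 0.13 are the correct inputs, which the article cannot settle. It also ignores unequal clinics: with CV 0.29 at 30 per clinic, DE = 1 + (1.0841 × 30 − 1) × 0.13 = 5.10 and the per-arm requirement is about 948.
- **That excluding pregnant couples leaves the sample short.** The article gives no pregnancy rate. The 70% response rate and the exclusion cite the same validation study, so the rate may already reflect the exclusion. If 10, 15 or 20% were lost on top, 1,120 would become 1,008, 952 or 896, all still above 888.
- **That the missing SD is a defect, or the word used for the 1,600 an error.** An article may leave the SD to the full protocol, and the Study design section makes clear that the 25 to 75 per clinic are invited.

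**Conclusion.** The clustering step is wrong as written. The stated inputs give 444 or 888, not 1,023, and 30 couples in each of 32 clinics give 960. The 1,462 is correctly derived from 1,023 and inherits the fault, and power is mislabelled as beta. This is a matter of moderate severity: a published sample size that its own inputs do not support, in a paragraph that is cheap to correct.

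A reader might infer that the trial is underpowered. The figures do not show that. The printed total exceeds both recomputed values, and the planned 1,600 invitations give about 84% power on the less favourable per-arm reading, with no extra enrolment called for. That figure assumes the back-calculated SD of 0.61, ICC 0.13, 70% response, equal clinic sizes, no further loss to pregnancy and a normal reference distribution. The margin is modest: about 81% with the assumed CV of 0.29, and about 80% if 15% of couples were also lost to pregnancy (952 couples, 29.75 per clinic, DE 5.06). A t reference on 30 degrees of freedom would lower that last figure to about 78%. This is a reason to state the power explicitly, not evidence of a shortfall.

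**What to change.** Rewrite the Sample size calculation paragraph so that its inputs and total agree:

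1. Replace the beta label with power 0.80 (beta 0.20).
2. State whether 93 is per arm or in total.
3. Give the cluster size and ICC actually used and the resulting design effect, including any allowance for unequal clinics, given that 25 to 75 are selected per clinic.
4. Correct whichever of 30, 0.13 or 1,023 is wrong. Only the sponsor's original calculation can settle which.
5. Restate the matching number of invitations. If the 70% response rate does not already cover the pregnancy exclusion, divide the requirement by 0.70 × (1 − expected proportion pregnant) and give the source of that proportion.
6. Report the power that 32 clinics and 1,600 invitations give for the 0.25 difference.

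The cost is one paragraph of text and a short recalculation. No change to the design or to enrolment follows.

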### Study design

In a cluster-randomized trial, the effects of a multifaceted approach on the level of patient-centered fertility care, patients’ QoL and the level of distress will be identified. To include a representative patient group for baseline measurement, clinics will be asked to extract the address files of all patients who underwent medically assisted reproduction in their clinics during the past 3 months (2011) from their diagnosis treatment combination coding system. Per clinic, 25 to 75 patients will be randomly selected depending on the clinic’s size. Participation is voluntary and anonymous. The couples will receive a letter with an invitation to participate. If they are willing, they complete an online questionnaire set, accessible by a personal code. Two weeks after the initial mailing, all patients will receive a reminder. Another 3 weeks later, nonresponders will receive a reminder with their personal codes and the additional option to complete a paper version of the questionnaire
[29].

Following baseline measurement, all 32 participating clinics will be randomly assigned to usual care (16 clinics) or to the multifaceted approach (16 clinics) with stratification for clinic size (large/medium/small) and IVF facilities (full licensed/intermediate/no IVF facilities).

After 1 year of intervention exposure, all clinics again extract the address files of all patients who underwent medically assisted reproduction in the last 3 months for the after measurement. The same questionnaire set will be used, which again have to be completed by both the women and the partners separately. Figure
1 illustrates the study design schematically.

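### The printed inputs (93 couples, 30 per clinic, ICC 0.13) do not lead to the stated 1,023 couples; at those inputs the error is conservative, but the calculation cannot be reproduced

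*Protocol article*

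**What the plan says.** The calculation is one paragraph in the protocol article, under Sample size calculation. It has three steps.

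- Unclustered number: "To detect a mean difference score of 0.25 between usual care and the multifaceted approach on patient-centeredness", with "α = 0.05, two-sided testing, β = 0.8", the article says that "at least 93 couples are required". It gives no SD and does not say whether 93 is per arm or for both arms together.
- Clustering: "Taking into account clustering of couples (30 couples/clinic) and a mean intracluster correlation coefficient of 0.13", it concludes that "1,023 couples have to be involved".
- Response: at an expected 70%, "at least 1,462 couples have to be invited at both baseline and after measurement".

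The same paragraph plans for at least 1,600 couples, chosen to give 25 to 75 patients per clinic, and presents the calculation as confirming that this is enough. Under Study design, the 32 clinics are to be "randomly assigned to usual care (16 clinics) or to the multifaceted approach (16 clinics").

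**The concern.** The clustering step prints its inputs and its result side by side, so a reader can check it, and it fails. The ratio 1,023/93 is exactly 11, and 1,023/186 is exactly 5.5. Ratios this round are not rounding noise, and neither is the inflation factor that 30 per clinic and an ICC of 0.13 produce.

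This is the only planning calculation in the article, and the invitation target for both surveys is built on it. As it stands, a reader cannot tell which of the printed figures (93, 30, 0.13 or 1,023) differs from what was used. Nor can the reader say what power the planned sample has.

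**Working it through.** **Inputs, all from Sample size calculation unless noted.** Difference 0.25; two-sided α 0.05; power 0.80 (printed as β = 0.8 and read here as power); 93 couples before clustering; m = 30 couples per clinic; ICC = 0.13; response 70%; 32 clinics, 16 per arm (Study design).

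**Step that reproduces.** 1,023 / 0.70 = 1,461.4, rounded up to 1,462. This agrees with the article.

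**Step that does not.** Design effect = 1 + (m − 1) × ICC = 1 + 29 × 0.13 = 4.77.

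| Reading of 93 | Couples needed | Invitations at 70% | Stated 1,023 is too high by |
|---|---|---|---|
| Total | 93 × 4.77 = 443.6, so 444 | 444 / 0.70 = 634.3, so 635 | 130% |
| Per arm (186 in all) | 186 × 4.77 = 887.2, so 888 | 888 / 0.70 = 1,268.6, so 1,269 | 15% |

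**Other routes that use only the printed m and ICC.** None gives 1,023:

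- 1 + m × ICC = 4.9 gives about 456 (93 total) or 911 (93 per arm).
- Doubling for two measurements gives 887 or 1,774.
- Adding one clinic per arm: 93 × 4.77 / 30 = 14.8, so 15 clinics per arm plus one is 16, and 16 × 30 × 2 = 960.
- Fixing 16 clinics per arm, m = n(1 − ICC)/(16 − n × ICC), gives 32 × 20.69 = 662 for n = 93 per arm, or 130 for n = 46.5 per arm.

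**What would be needed to reach 1,023.**

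- 93 per arm: ICC = (5.5 − 1)/29 = 0.155 at m = 30; or m = 1 + 4.5/0.13 = 35.6 at ICC 0.13; or, with design effect 1 + ((CV² + 1)m − 1) × ICC, a cluster-size CV of √(35.6/30 − 1) ≈ 0.43.
- 93 total: ICC = (11 − 1)/29 = 0.345, or m = 1 + 10/0.13 = 77.9.
- Dividing 4.77 by (1 − ICC) gives 186 × 4.77/0.87 = 1,020. This is close, but it is not the usual inflation.

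The per-arm reading needs much the smaller departure. That makes it more plausible but does not establish it.

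**What the planned sample delivers at ICC 0.13.**

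- If 1,600 means couples invited, 1,600 × 0.70 = 1,120 respondents, or 35 per clinic. The design effect is 1 + 34 × 0.13 = 5.42. With 93 per arm, 186 × 5.42 = 1,008.1, so 1,009 respondents and 1,009/0.70 = 1,441.4, so 1,442 invitations. Both are below plan. Power at 1,120 is about 84%.
- If 1,600 means respondents, that is 50 per clinic. The design effect is 7.37, and 186 × 7.37 = 1,371, again below 1,600.
- At 1,023 respondents spread over the 32 clinics, normal-approximation power is about 83% with 93 per arm and above 98% with 93 as the total.

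These power figures use an SD back-calculated from 93, because none is printed: 0.25 × √(93/2)/2.8016 ≈ 0.61 if per arm, about 0.43 if total.

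**The case against.** The best defence is that 1,023 may be right and only its explanation incomplete. Clinics contribute 25 to 75 patients, so cluster sizes are unequal and 4.77 is a lower bound on the design effect at a mean of 30. The article gives no size distribution, so any figure is an assumption. With 93 per arm, sizes uniform over 25 to 75 give about 948, equal thirds at 25, 50 and 75 give about 1,008, and an even split between 25 and 75 gives about 1,069. The stated 1,023 lies inside that range. A journal article also condenses, and the full calculation may contain such an allowance.

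This defence shows that 1,023 could be defensible, and for that reason the figure should not be called wrong in itself. It does not rescue the step as printed. The article names 30 and 0.13 as what was taken into account and mentions no allowance for unequal sizes. Having chosen to print inputs and a result, it should print ones that agree.

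A related observation, that 30 couples in 32 clinics make 960 rather than 1,023, carries little weight. Thirty can be a planning average, and 1,023/32 is about 32 per clinic.

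A reader might also infer that an ICC of 0.15 was really used, since 5.5 = 1 + 30 × 0.15, and that the trial is therefore short of patients. The document does not support this. It prints 0.13 and nowhere 0.15. The match also relies on 1 + m × ICC, whereas the usual formula gives 0.155, and other unprinted inputs fit equally well.

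**Conclusion.** The step from 93 to 1,023 couples does not follow from the printed cluster size and ICC. The printed inputs give 444 couples and 635 invitations, or 888 and 1,269, against the stated 1,023 and 1,462. The larger discrepancy of 130% requires reading 93 as the total; on the per-arm reading it is 15%.

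A reader might conclude that the claim of a sufficient sample is unsupported. It is not: at the printed inputs the error is on the safe side, and the planned 1,600 exceeds the invitation target on either reading of 93. That conclusion depends on the printed ICC of 0.13 being the one that applies, and on 93 itself, which cannot be checked without an SD. The point concerns a calculation that cannot be reproduced. It should be fixed, but it does not call the design into question.

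**What to change.** Rewrite the paragraph so that every step reproduces:

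1. State the SD behind 93 and whether 93 is per arm or for both arms.
2. State the ICC, the cluster size and any allowance for unequal clinic sizes (with its CV) that were actually used.
3. Restate the required number of respondents, the invitation target and the power of the planned sample. State whether 1,600 counts couples invited or couples responding. Label 0.8 as power rather than β.

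If 93 per arm and ICC 0.13 are confirmed and 1,600 means invited, using 35 respondents per clinic gives the 1,009 respondents and 1,442 invitations derived above, within about 1.4% of the stated figures.

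The cost is one reworded paragraph, which can be settled before the after-measurement mailing. No extra patients are needed, and neither the design nor the analysis changes.
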